### Data Analysis

#### Quantitative Analyses

The statistical package SPSS (version 29; IBM Corp) will be used for all statistical analyses. Descriptive statistics will be used to provide an overview of the demographic variables. Given the exploratory nature of this study and the limited sample size, our analysis involves looking at the data from multiple perspectives. The aim is to uncover patterns and relationships that could inform the development of hypotheses for future studies.

To answer the research questions, we will first calculate descriptive statistics for changes in frailty levels between 2 time points, using mean and SD or median and IQR for a skewed distribution. This will be followed by paired comparisons using either 2-tailed *t* test or the Wilcoxon test. We will also examine the association between the changes in frailty and baseline levels by plotting and estimating correlation coefficients (Pearson and Spearman). We will further assess changes in functional variables and the bivariate associations between these changes and the change in frailty.

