## Introduction

Across the globe, the population is aging rapidly. There are around 1.4 billion people aged 60 years and older in the world today, and this figure will double by 2050 [1]. Norway is no exception to this demographic transition. It is anticipated that the number of people aged 65 years and older will exceed the population aged 0-19 years by 2030 [2]. As is widely known, the older segment of the population tends to have a higher prevalence of chronic diseases and disabilities [3,4]. This implies that the demographic shift could come at a great cost to older adults themselves and society [3,5]. Direct challenges at the societal level may include a strain on public finances and the welfare system, increased demand for health services, and rising health care costs [6,7].

One way to mitigate the impacts of an aging population is to support aging in place [8,9]. The term “aging in place” refers to meeting an older adult’s needs and supporting them to live independently or with some assistance in their own home for as long as possible [8]. Most older adults prefer to live at home because it enables them to maintain their independence, autonomy, and identity, as well as their connection to social support [10]. In addition to being the preferred choice for many older adults, aging in place is viewed as a cost-effective strategy for addressing the aging population’s needs, as it can reduce the expenses associated with institutional care [11]. Given these positive effects, encouraging older adults to continue living at home could be an essential part of the solution to meeting the challenges of population aging.

Many older adults are able to live independently without much support; others, however, may have age-related issues that prevent them from aging in place [12]. These age-related issues often lead to frailty, resulting in increased functional limitations, increased risk of falls, disability, institutionalization, hospitalization, and mortality [13,14]. As frailty progresses, efforts to mitigate, manage, or reverse this decline become increasingly difficult to implement [15]. Hence, there is a broad consensus on the importance of assessing frailty [14,16,17], particularly in relation to older adults aged 70 years and older [16,18]. In general, early assessment of frailty can prevent, reduce onset, or slow its progression in older adults [19], contributing to better quality of life and healthy aging [18,20].

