### Recruitment

Participant recruitment was conducted in collaboration with 3 health and welfare service departments in a municipality in the western region of Norway between February 1 and June 26, 2023. Health care professionals purposively selected participants according to the eligibility criteria. During their initial phone contact with potential participants, health care professionals used their professional judgment to assess the individual’s ability to understand the research project and provide informed consent to participate.

Subsequently, health care professionals asked a designated research team member, a nurse with experience in mental health, to obtain informed consent from those who meet the initial criteria. To ensure consistency in the process, the same nurse visited all potential participants for the consent process. Potential participants were then given time to consider this information before giving their written consent.

The design of our health needs assessment package includes a cognitive assessment. This approach ensures that participants identified with cognitive impairment in the first assessment are not included in the second assessment.

We aim to enroll 40 participants in the quantitative phase of this study, in line with the agreement made with the municipality at the beginning of the project, taking into account their resource limitations. In the next phase, which uses a qualitative approach, we plan to invite all 40 participants for an interview, with the actual number of interviews conducted depending on the participants’ consent to participate. To capture diverse perspectives, we will strive to include a group of home-living older adults who differ in terms of age, gender, marital status, living situations, and health care needs.

The aforementioned sample size takes into account the limited resources available for the project, including budget constraints, personnel resources, and time limitations, while ensuring the collection of meaningful data to address the research questions.

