### Data Collection

To respond to the diverse needs of older adults, we have interprofessional teams consisting of registered nurses, physiotherapists, or occupational therapists to carry out the health needs assessments. The assessment is conducted twice at the participant’s home. To facilitate successful implementation, we provided simulation-based training and debriefings. We have also produced webinars available in Norwegian to enhance learning. The link to the webinars can be provided upon request. Our study is ongoing, so we will publish it upon completion.

The interprofessional teams will use an iPad (Apple Inc) to administer assessments covering the various factors—physical (mobility and sensory), cognitive, psychological (depression), social (loneliness), and behavioral (alcohol consumption). The collected data will be registered electronically and directly submitted to Services for Sensitive Data (*Tjenester for Sensitive Data* [TSD]) for secure storage and processing.

After the initial assessment, interprofessional teams will collaboratively review the results to determine whether, and to what extent, the older adult is eligible for assistance and to determine what type of support is available and appropriate for the individual [33]. Examples of such support include practical help with everyday tasks, provision of medical emergency alarms, access to walking aids, recommendations for physiotherapy sessions, referrals to hearing or vision centers, encouragement to participate in senior activity centers, and facilitating contact with primary care physicians.

After 5 months, the same interprofessional teams will conduct the second health needs assessment to determine whether the support provided at the first assessment is suitable for helping participants maintain their quality of life.

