### Outcome Measures

This study has two primary outcome measures: (1) identifying changes in frailty levels of home-living older adults over a period of 5 months and (2) assessing any observed changes in functions from t1 to t2 and how these changes relate to the level of frailty.

In addition to the primary outcome measures, this study will also evaluate the feasibility of the health needs assessment. Emphasis will be placed on the acceptability of the assessment among older adults and their informal caregivers, as well as the practicality of implementation in relation to time and resource constraints.

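### The paired frailty change covers only people reassessed at month 5, so it probably understates worsening by an amount the article gives no means to size

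*Protocol article*

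**What the plan says.** All places are in the protocol article.

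- **Outcome Measures** gives the first primary outcome as "identifying changes in frailty levels of home-living older adults over a period of 5 months".
- **Quantitative Analyses** summarises it by "descriptive statistics for changes in frailty levels between 2 time points" and then tests it: "This will be followed by paired comparisons using either 2-tailed *t* test or the Wilcoxon test". The same section relates the change in frailty to its baseline level and to changes in function.
- **Data Collection** fixes the place of measurement: "The assessment is conducted twice at the participant’s home". The second visit follows after 5 months.
- **Introduction** lists what frailty results in, including "increased risk of falls, disability, institutionalization, hospitalization, and mortality". Table 1 adds that the CFS, the frailty measure used here, strongly predicts mortality and length of hospital stay.
- **Inclusion Criteria** admit people aged 75 or older who have applied for municipal services, and also people followed up after hospital, rehabilitation or emergency care. **Exclusion Criteria** keep out people in palliative care.
- **Recruitment** adds a separate planned loss: people found cognitively impaired at the first assessment do not have the second.
- **Strengths and Limitations** names the small sample, the missing control group, confounding, habituation and possible underrepresentation. It does not name loss between the two assessments.

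**The concern.** A paired test uses only people with both scores. The second score is to be obtained at home, and the events that would prevent a home visit for good (death, a permanent move to an institution) are among those the article attributes to frailty. Loss from the analysis is therefore likely to be related to the outcome being measured.

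Two results are affected. The headline change in frailty would describe people still available for reassessment, and would probably look more stable than the course of everyone enrolled. The correlations between change in function and change in frailty would lose the same people. The article's rationale is ageing in place and its second visit is meant to judge whether the support given was suitable, so people who die or leave home for good matter to the question.

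**Working it through.** **1. The plan's own figure.** The only planning number is the sample size: "We aim to enroll 40 participants in the quantitative phase of this study". Its basis is practical: "The aforementioned sample size takes into account the limited resources available for the project". No alpha, power, effect size, SD or attrition rate is given, so there is no calculation to reproduce. Every loss figure below is an assumption.

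**2. Who supplies a pair.** Reading Data Collection and Quantitative Analyses together:

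| Situation at month 5 | Second score under the text as written |
|---|---|
| At home | Yes |
| Temporarily in hospital | Perhaps, if the visit is delayed |
| Permanently in an institution | Unlikely, unless assessed away from home |
| Dead | No |
| Declined | No |
| Cognitive impairment found at first assessment | No, by design |

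The third and fourth rows are the ones tied to the course of frailty.

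**3. Effect on the share who worsened.** Assume 40 enrolled, 4 lost to death or permanent institutional care, 36 reassessed, and 8 of those 36 worsened.

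- Observed pairs: 8/36 = 22%.
- If a fraction q of the 4 lost worsened, the share among all enrolled is (8 + 4q)/40.
- q = 1: 12/40 = 30%.
- q = 0.5: 10/40 = 25%.
- q = 8/36: 8.89/40 = 22%, so no bias.

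Holding the 22% rate among those reassessed and counting every loss as worsened, (8/36 × (40 − L) + L)/40 gives 26% for L = 2 and 34% for L = 6. The rise follows from counting losses as worsened. It illustrates the issue and estimates nothing.

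**4. Effect on the mean change.** With k of N lost:

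mean change in all enrolled − mean change in those reassessed = (k/N) × (mean change in the lost − mean change in those reassessed).

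This presumes that a CFS change can be given to the lost, which for death is a convention. For an assumed gap of 1 to 3 CFS levels:

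| Lost, k of 40 | k/N | Understatement, CFS levels |
|---|---|---|
| 2 | 0.05 | 0.05 to 0.15 |
| 4 | 0.10 | 0.10 to 0.30 |
| 6 | 0.15 | 0.15 to 0.45 |
| 8 | 0.20 | 0.20 to 0.60 |

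The bias is zero if nobody is lost or if the lost change no more than the others.

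**5. Precision is a lesser matter.** Assuming two-sided 5% and 80% power, a paired t test detects a standardised change of 0.454 with 40 pairs, 0.480 with 36 and 0.511 with 32. Losing a few pairs costs little precision, so the issue is who is lost.

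**6. Effect on a sign analysis.** In the example of step 3, suppose 8 of the 36 also improve. The balance is 8 worse against 8 better. Ranking the 4 losses worst makes it 12 against 8. The exact two-sided sign test then gives 2 × P(X ≥ 12 of 20) = 2 × 263,950/1,048,576 = 0.50. The added analysis changes the description more than the significance.

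**The case against.** The strongest reply is that the article never says anyone is dropped. It names a test and a usual place of visit; handling of death and drop-out commonly sits in a full protocol or analysis plan that is not shown. A hospital stay may only delay a visit. The CFS rests on clinical judgement and, per Table 1, has been used in emergency and intensive care, so it can be rated away from home. Change among people still living at home is also a coherent target. The study is exploratory and already urges caution.

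Much of this stands. Exclusion is an inference from the home visit and the paired test, and a temporary admission should not be counted as a loss. The exclusion of palliative care should lower expected mortality, and some listed services, such as alarms and activity centres, can be used by people with modest needs.

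A reader might also infer that those lost are the people with the largest change. The documents do not show that. The Introduction and Table 1 link frailty to these events, which directly supports losing people who are frailer; it supports losing those who change most only indirectly.

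What does not stand is leaving it all to an analysis plan. Such a plan cannot recover a month-5 status or an off-home rating that was never collected. Nor does the article limit its objective to those still at home at month 5, and general caution about sample size and controls does not tell the reader that the pairs are selected.

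**Conclusion.** The point holds in a limited form. As written, the first primary outcome is described for those who can be reassessed, and people who die or permanently leave home by month 5 are likely to be absent from it. The paired result probably understates worsening, on the assumption that those lost worsen more than those reassessed. The article's account of frailty makes that plausible without proving it.

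The size cannot be stated, since no attrition rate is given. The move from 22% to 30% assumes 4 of 40 lost and all counted as worsened; the 0.05 to 0.60 CFS levels assume 5% to 20% lost and a gap of 1 to 3 levels. A reader might take either as the true shortfall, or conclude that the plan deliberately excludes these people; the text supports neither reading. For an exploratory study this is a worthwhile, inexpensive improvement and does not undermine the design.

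**What to change.** 1. For every enrolled participant, record status at month 5: at home, temporarily in hospital, in an institution, dead, declined, or removed for cognitive impairment at the first assessment. Tabulate it by baseline CFS.
2. Attempt the CFS rating wherever a living participant who remains in the study is residing, and use that score in the paired analysis.
3. Keep the observed-pairs test and state that it applies to those reassessed.
4. Beside it, show the proportion who worsened, moved permanently to institutional care or died, with its denominator.
5. Add a supplementary sign or rank analysis in which death ranks worst, together with only those permanent moves for which no CFS could be obtained. A person who moved and was rated keeps the rated score, so nobody is counted under both rules.
6. Report those who declined or were removed for cognitive impairment separately, without assigning them a rank.

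**Cost:** one status field per participant from the partner municipality, possibly a few ratings away from home, one table and one extra analysis. The Results section says second assessments were still under way when the article was written. Status can be filled in afterwards; a rating that was not made at month 5 cannot. The supplementary result is a composite that mixes CFS change with death and institutional care, which is why the paired result stays beside it. Consent or approval wording for the status field may need a check.

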### Study Sample

#### Inclusion Criteria

To be eligible for the study, the older adults must be aged 75 years or older and have applied for municipal health and care services. These services may include medical emergency alarms, senior activity centers, home-based nursing services, and practical assistance with daily chores. In addition, older adults who received follow-up care after a hospital stay, were discharged from rehabilitation, or received emergency medical care are also eligible.

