**Behavioral function**			
	Alcohol consumption	For a brief assessment of alcohol consumption, we will use the AUDIT^f^ developed by the World Health Organization [60]. Our study will use AUDIT-4, which consists of 3 questions from AUDIT-C and the 10th item of the original scale [61]. In terms of reliability and validity, previous research with different samples has shown that AUDIT-4 has good internal consistency, criterion validity, and convergent validity [62,63].	
Assessment of frailty			To assess frailty, we will use the CFS^g^. The CFS, a tool based on clinical judgment, assesses key areas such as multimorbidity, cognition, and other functional areas [64]. CFS has been shown to be a strong predictor of several outcomes, including falls, length of hospitalization, multimorbidity, and mortality [65]. The CFS was translated into Norwegian by Rostoft et al [66] and has been used to assess frailty in various settings in Norway, including emergencies and intensive care [67,68]. Its simplicity and predictive power in assessing physical health and potential outcomes for frail older adults [17,69] make it an appropriate choice for use in municipal health care settings.

^a^SPPB: Short Physical Performance Battery.

^b^KAS: *Kombinert Alvorlig Sansesvikt* (Combined Serious Sensory Impairment).

^c^KROSS: *Kompetanse om Rehabilitering Om Syn og Slag* (Competence, Rehabilitation of Sight after Stroke).

^d^GDS: Geriatric Depression Scale.

^e^UCLA: University of California, Los Angeles.

^f^AUDIT: Alcohol Use Disorders Identification Test.

^g^CFS: Clinical Frailty Scale.

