## Discussion

### Principal Considerations

Studies have documented that frail older adults have an elevated risk of negative health outcomes [13,14]. Early assessment of frailty in older adults is, therefore, crucial, and is recommended. Despite its recognized importance, assessing frailty is not considered a standard clinical practice in many health care systems [18], including in Norway [72]. This situation is understandable as such an assessment often requires significant resources, which many health care facilities lack [73].

Our study is carefully designed to reflect real-world applications and settings, with a particular focus on municipal health care in Norway, where health care professionals tend to have heavy workloads. These conditions pose a challenge to incorporating additional tasks, such as a frailty assessment, into routine health needs assessments. As mentioned earlier, older adults typically turn to their local municipality for home care services and health care professionals make home visits to assess their care needs. This assessment process uses the standardized tool (The Norwegian Information System for the Nursing and Care Sector [*Individbasert pleie- og omsorgsstatistikk*; IPLOS]), which was developed to optimize care needs assessments in Norway [33]. Despite being a standardized tool, IPLOS has been criticized for being too subjective, as assessments appear to vary widely among health care professionals [74].

In response to these challenges, we aim to refine the health needs assessment process to improve objectivity and consistency, and to highlight the critical needs to incorporate frailty assessments into routine municipal care practices. The path begins with selecting appropriate measurement tools that are meaningful and practical, and training interprofessional teams to implement them. Part of this training process includes the task of conducting assessments and discussing the results to make informed decisions.

Beyond integrating assessments, our study aims to shed light on the dynamic nature of frailty and provide a deeper understanding of the factors that impact its progression. This insight could potentially help older adults and their informal caregivers to manage frailty. Additionally, it can better prepare health care professionals to develop and implement strategies aimed at delaying and mitigating the progression of frailty.

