### Strengths and Limitations

This study has several strengths. First, it deepens our understanding of frailty as a complex condition and highlights how levels of frailty and related functional changes can differ. Moreover, because the study is designed to reflect the real-world settings and applications, it can help improve health care practices in the municipal sector. The involvement of local stakeholders in the municipality from the planning to the implementation phase ensures that the study remains relevant and applicable, thereby facilitating the translation of knowledge into practice. Additionally, the inclusion of home-living older adults’ and their informal caregivers’ perspectives can help facilitate improvement in the feasibility of the assessment.

As with other studies, this study has its limitations, particularly with regard to the relatively small sample size and the absence of a control group. This could lead to misinterpretation of the observed changes, either in the support or services for participants, other confounding factors, or due to a habituation effect over the 5-month period. Consequently, this limitation may also potentially impact the internal validity of the study, as well as the construct validity of the study [75]. To address this challenge, we will carefully compare our findings with those of previous studies investigating similar approaches to aiding the interpretation of outcomes.

Despite its inherent limitations, this study will serve as an important first step in developing a more systematic health needs assessment for home-living older adults and the development of health promotion strategies that can improve these older adults’ quality of life.

Nonetheless, the results should be interpreted with caution due to the absence of a control group, the limited sample size, and the potential underrepresentation of all home-living older adults. These limitations suggest that the results indicate possible correlations and patterns, rather than confirming a definite relationship or establishing specific cause-and-effect relationships.

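### The planned correlation of frailty change with baseline level is pulled negative by the shared first rating, so zero is the wrong reference value

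*Protocol article*

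**What the plan says.** Under Quantitative Analyses, frailty change is first summarised and compared between the two visits. The plan then continues: "We will also examine the association between the changes in frailty and baseline levels by plotting and estimating correlation coefficients (Pearson and Spearman". The article does not say which baseline variable is meant. Functional variables enter only in the following sentence, so baseline frailty is the natural reading.

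Other statements that bear on the point:
- Size (Recruitment): "We aim to enroll 40 participants in the quantitative phase of this study". The number rests on resources, and fewer pairs are likely because "participants identified with cognitive impairment in the first assessment are not included in the second assessment".
- Measure (Table 1): "The CFS, a tool based on clinical judgment". No reliability, SD or correlation between visits is given.
- Entry (Inclusion Criteria): "older adults who received follow-up care after a hospital stay, were discharged from rehabilitation, or received emergency medical care are also eligible".
- Design (Strengths and Limitations): the article concedes "the relatively small sample size and the absence of a control group".
- Ambition (Principal Considerations): "our study aims to shed light on the dynamic nature of frailty and provide a deeper understanding of the factors that impact its progression".

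**The concern.** Change is the second rating minus the first. A participant rated too frail by chance at the first visit has a high baseline and, on average, an apparent improvement at the second. One rated too fit shows the reverse. A negative correlation therefore arises even when nobody's frailty changes. Ranking the data does not remove the shared term, so reporting Spearman beside Pearson gives no protection.

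The setting makes the artefact easy to misread. The CFS rests on judgment, so some rating error is to be expected. People may enter shortly after acute care, perhaps at a poor moment. Support is arranged after the first assessment, and there is no comparison group. A negative coefficient could pass for evidence that the frailest benefited most, and a hypothesis-generating study could hand that pattern on to its successors.

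**Working it through.** There is no figure in the plan to reproduce.

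**Inputs.** n = 40 is from Recruitment. Everything else is assumed: two-sided alpha 0.05, rho from 0.5 to 0.9, 32 pairs as a low case and, for whole-level simulations, CFS levels 1 to 9, mean 4.5 and true-score SD 1.1. Errors at the two visits are taken as independent.

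**1. Expected coefficient.** With SDs s1 and s2,

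r = (rho·s2 - s1) / sqrt(s1² + s2² - 2·rho·s1·s2).

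If s1 = s2, this is -(1-rho)/sqrt(2(1-rho)) = -sqrt((1-rho)/2). At rho 0.9 it is -sqrt(0.05) = -0.22, and at rho 0.5 it is -sqrt(0.25) = -0.50. It is zero only if s2/s1 = 1/rho, for example 1.25 at rho 0.8.

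**2. Critical value.** |r| = t/sqrt(n-2+t²). For n = 40, 2.024/sqrt(38+4.098) = 0.312. For n = 32 it is 0.349. The expected r alone passes the critical value when rho is below 1 - 2(0.312²), about 0.81, for n = 40, and below about 0.76 for n = 32.

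**3. Rejection with no true change.** Pearson, 3,000 simulated studies per setting:

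| rho | expected r | n = 40, continuous | n = 40, whole levels | n = 32, continuous |
|---|---|---|---|---|
| 0.9 | -0.22 | 30% | 40% | 24% |
| 0.8 | -0.32 | 51% | 61% | 44% |
| 0.7 | -0.39 | 72% | 77% | 60% |
| 0.6 | -0.45 | 84% | 86% | 75% |
| 0.5 | -0.50 | 93% | 94% | 86% |

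For whole levels, rho refers to the scores before rounding. Repeat runs differ by a point or two; the n = 40 continuous entry at rho 0.9 ranged from 28% to 30%. Spearman at n = 40 rejects in 27% to 89% (continuous) and 38% to 92% (whole levels).

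**4. True change that varies independently of baseline.** Set the baseline variance to 1, of which 0.9 is true and 0.1 is error, and let true change have variance 0.3.
- Second-visit variance is 1.3, the covariance is 0.9, and rho = 0.9/sqrt(1.3) = 0.79.
- The variance of change is 0.3 + 2(0.1) = 0.5, and its covariance with baseline is -0.1.
- So r = -0.1/sqrt(0.5) = -0.14. The equal-variance formula at the same rho gives -sqrt(0.21/2) = -0.32.
- Simulated rejection is 14% to 15% (whole levels: r -0.20, 23%).
- With reliability 0.95, r = -0.05/sqrt(0.4) = -0.08 and rejection is 7% (whole levels 15%).

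For reliability R, both cases follow from one expression: expected r = -(1-R)·s1/SD(change).

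**5. Change against the mean of the two ratings (Oldham).** With no true change, mean r is about zero and rejection is 3.7% to 5.9%. In the step 4 example:
- The covariance of change with the mean is (1.3-1)/2 = 0.15, and the variance of the mean is (1+1.3+1.8)/4 = 1.025.
- So r = 0.15/sqrt(0.5×1.025) = +0.21, with 24% to 26% rejection (whole levels 20%).
- With reliability 0.95, r = 0.15/sqrt(0.4×1.05) = +0.23, with 31% rejection (whole levels 24%).

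This version is therefore biased in the opposite direction when people truly change by different amounts.

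**The case against.** Four points are fair.

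- **No test is stated.** The plan speaks of plotting and estimating. Two-tailed testing is attached only to the "paired comparisons using either 2-tailed" analysis. A reader might infer an invalid significance test, but the article does not specify one. The bias nevertheless lies in the coefficient, which the plan does commit to.
- **A significant negative result is not assured.** A reader might infer that the study will show one. At rho 0.9 with continuous scores fewer than a third of null studies would, and less often still if real change varies. The article gives no reliability with which to place the study in the range.
- **The obvious replacement has its own bias.** A reader might conclude that change against the mean must replace the planned analysis. Step 5 shows it can mislead more often than the raw coefficient when true change differs between people, which is something this study sets out to look for.
- **The analysis is supplementary.** The research questions and primary outcomes concern change in frailty, change in function and how function relates to frailty. The study is declared exploratory, and Strengths and Limitations disclaims causal conclusions.

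That last caution names sample size, missing controls, confounding and habituation. It does not name regression to the mean, and calling a result only a possible correlation does not help when the correlation is produced by the calculation itself.

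**Conclusion.** The concern holds with limits. If the baseline is baseline CFS, the planned coefficients are biased negative and should not be judged against zero. With equal variances and no true differences in change, the reference value runs from -0.22 to -0.50 for rho 0.9 to 0.5, and a nominal 5% test at n = 40 would reject in about 28% to 93% of studies. These figures rest on an assumed rho and alpha, and on rating errors that are independent between visits. They shrink if true change varies independently of baseline. If baseline function was meant, the frailty score is not shared and this coupling does not arise. It should be fixed, but it does not threaten the main before-after comparison.

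**What to change.** Amend the sentence under Quantitative Analyses as follows:

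1. Name the baseline variable.
2. If it is baseline CFS, present the plot and both coefficients descriptively, with no p-value against zero.
3. Beside them, show the value expected from regression to the mean over a stated range of rho or CFS reliability. The equal-variance form is -sqrt((1-rho)/2); the form allowing varying true change is -(1-R)·s1/SD(change).
4. Add the correlation of change with the mean of the two ratings (equivalent to the Pitman-Morgan comparison of variances) as a sensitivity analysis, not as an unconditional replacement. State that it assumes equal error variance at the two visits and is biased positive when true change differs between participants.
5. Draw a conclusion about dependence on baseline only if both analyses agree, with the raw coefficient read against its reference value.
6. Name regression to the mean in Strengths and Limitations.

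No new data are needed. The cost is one extra analysis and a more guarded conclusion.
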